### Sample size calculation

After randomization of 75 participants, the sample size calculation was carried out by an independent statistician to base it on realistic data.

Sample size was calculated with SPSS 17.0, using the mixed-model ANOVA procedure described by Aberson [44].

Alpha was set at 0.05, power at 0.80 and the baseline-end correlation at 0.90. A clinically relevant difference between the treatment groups is 5% weight loss [3]. Mean weight at the start of the treatment is about 110 kg, with a standard deviation of 22, this equals an effect size of d = 0.25.[45] With this power calculation we estimate that we need 52 patients in each group. Anticipating a dropout rate of 25%, we aim for a total sample size of 140.

For the most important secondary outcomes we calculated the detectable difference with the sample size of n=104, alpha 0.05 and power 0.80 (Table 2). The detectable differences are quite small, so the aimed sample size seems adequate to analyse at least these secondary outcomes.

**Table 2 T2:** Power calculation secondary outcomes

**Secondary outcome:**	**SD:**	**Detectable difference:(n = 104, β=0.8 α=0.05)**
Waist circumference	11	2.75 cm
Blood pressure sys/dias	20/20	5/5 mmHg
Total cholesterol	1.4	0.35 mmol/l
LDL cholesterol	1.0	0.25 mmol/l
HDL cholesterol	0.7	0.2 mmol/l
Triglyceride	3.0	0.75 mmol/l
HbA1c	12	3 mmol/mol
Insulin	50	12.5 IU
Depression (HADS score 0–21)	3	0.75
Anxiety (HADS score 0–21)	4	1.0
Self esteem (RSE score 10–40)	5	1.25
Fatigue (CIS score 8–56)	13	3.25
Concentration (CIS score 5–35)	8.5	2.1
Motivation (CIS score 4–28)	6	1.5
Activity (CIS score 3–21)	5	1.25
Quality of life (EuroQol 5D score 1–3)	0.5	0.125
Quality of life (EuroQol VAS 1–100)	21	5.25

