### Randomization

Groups of 20 patients will start with a VLCD concomitantly. After 8 weeks of VLCD, the patients who lost ≥5% of bodyweight are randomly assigned to either or the intervention group (usual care + CPI) or the control group (usual care) with an allocation ratio of 1:1. The stratified randomization is computer controlled, carried out by a secretary and supervised by a statistician, who are both not involved in the trial. The reason for a stratified randomization is to avoid an unsuccessful randomization with regard to weight loss during the VLCD. It is not possible to correct afterwards in the analysis, as it is the primary outcome measurement. We defined the following strata (based on clinical experience):

1. 5% - 7,5%

2. 7,5% - 10%

3. >10% weight loss after 8 weeks of VLCD.

The statistician generates the allocation sequence and hands it over to the secretary of the department of Medical Psychology and Psychotherapy, who is not involved in the study, to guarantee allocation concealment. The secretary assigns the participants to their group and makes a list for [name], who will plan their study appointments.

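### Every detectable difference in Table 2 is 0.25 SD, which requires weight's 0.90 correlation for every secondary outcome; the pilot contradicts it for the ten outcomes it covers (LDL only marginally).

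*Protocol article*

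**What the plan says.** The section Sample size calculation works out the sample for weight "using the mixed-model ANOVA procedure described by Aberson". Its error rates and correlation come first: "Alpha was set at 0.05, power at 0.80 and the baseline-end correlation at 0.90". The target difference follows: "A clinically relevant difference between the treatment groups is 5% weight loss". An effect size d of 0.25 is then derived from the distribution of weight: "Mean weight at the start of the treatment is about 110 kg, with a standard deviation of 22, this equals an effect size of d". The result is "With this power calculation we estimate that we need 52 patients in each group", raised for dropout: "Anticipating a dropout rate of 25%, we aim for a total sample size of 140".

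The section then turns to the secondary outcomes. Table 2 gives an SD and a detectable difference for each, at a total of 104 patients, alpha 0.05 and power 0.80. No correlation is given for any of them; 0.90 is the only one in the section. The section ends: "The detectable differences are quite small, so the aimed sample size seems adequate to analyse at least these secondary outcomes".

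Table 5 (Data/results pilot study) reports means at baseline and 4 months for 13 patients, with paired 95% confidence intervals for the change. It covers weight and ten of the Table 2 outcomes.

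**The concern.** Weight tracks closely within a person, so 0.90 is plausible for it. HbA1c, blood pressure, triglycerides, insulin dose and mood scores usually track less closely, especially across a crash diet with medication changes. A table in which every outcome has the same standardised detectable difference suggests that weight's correlation was reused without a check.

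The article's secondary objectives include glycaemic control, cardiovascular risk and psychological variables. If the detectable differences are understated, a reader of a null HbA1c or blood pressure result could take the trial to have had 80% power for effects that it had little chance of finding.

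**Working it through.** **1. Reproduce the primary figure.** Inputs: difference 5% of 110 = 5.5 kg, SD 22, correlation r = 0.90, alpha 0.05 (two-sided assumed), power 0.80, allocation "with an allocation ratio of 1:1". With two time points, the group-by-time test of a mixed ANOVA is a comparison of change scores.

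- SD of change = SD × √(2(1 − r)) = 22 × √0.2 = 9.84 kg.
- The t-based sample size is 52 per arm (power 0.806), as stated. With dropout, 104/0.75 = 139, stated as 140.

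**2. Find what Table 2 assumes.** Difference divided by SD is 0.25 throughout (HbA1c 3/12, blood pressure 5/20, depression 0.75/3). Two entries differ only by rounding: HDL 0.175 shown as 0.2, and concentration 2.125 shown as 2.1.

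With 52 per arm the detectable difference is 0.5547 × SD of change. In SD units:

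| r | change score, 0.5547√(2(1 − r)) | baseline-adjusted, 0.5547√(1 − r²) |
|---|---|---|
| 0.90 | 0.248 | 0.242 |
| 0.80 | 0.351 | 0.333 |
| 0.50 | 0.555 | 0.480 |
| 0 | 0.784 | 0.555 |

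Only r of about 0.90 gives 0.25 SD.

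**3. Read the SD of change from the pilot.** For a paired interval with n = 13, SD of change = half-width × √13 / 2.179. For HbA1c: 9.45 × 3.606 / 2.179 = 15.6. The value needed at r = 0.90 is Table 2's SD × √0.2, here 12 × 0.447 = 5.4. The implied correlation is 1 − SDchange²/(2 SD²).

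| Outcome | SD of change (lower 95% limit) | Needed at 0.90 | Implied r |
|---|---|---|---|
| Weight | 5.96 (4.27) | 9.84 | 0.96 |
| LDL | 0.66 (0.47) | 0.45 | 0.78 |
| Waist | 7.45 (5.34) | 4.92 | 0.77 |
| Diastolic BP | 14.2 (10.2) | 8.94 | 0.75 |
| Total cholesterol | 1.24 (0.89) | 0.63 | 0.61 |
| Triglycerides | 3.39 (2.43) | 1.34 | 0.36 |
| Systolic BP | 25.7 (18.5) | 8.94 | 0.17 |
| HbA1c | 15.6 (11.2) | 5.37 | 0.15 |
| Depression | 4.30 (3.09) | 1.34 | −0.03 |
| Insulin | 72.3 (51.9) | 22.4 | −0.05 |
| HDL | 1.32 (0.95) | 0.31 | −0.79 |

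For all ten secondary outcomes even the lower limit exceeds the needed value. For LDL the margin is within rounding of the published interval: a half-width of 0.35 instead of 0.40 would give a lower limit of about 0.42, below 0.45. Weight supports 0.90.

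**4. Recompute the detectable differences (52 per arm, 80% power).** Negative implied correlations are set to zero for the adjusted analysis.

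| Outcome | Table 2 | Adjusted to change score | Ratio | Power at the Table 2 value |
|---|---|---|---|---|
| LDL (mmol/l) | 0.25 | 0.35-0.37 | 1.4-1.5 | 48-52% |
| Waist (cm) | 2.75 | 3.9-4.1 | 1.4-1.5 | 46-51% |
| Diastolic BP (mmHg) | 5 | 7.3-7.9 | 1.5-1.6 | 43-48% |
| Total cholesterol (mmol/l) | 0.35 | 0.62-0.69 | 1.8-2.0 | 30-36% |
| Triglycerides (mmol/l) | 0.75 | 1.55-1.88 | 2.1-2.5 | 20-27% |
| Systolic BP (mmHg) | 5 | 10.9-14.3 | 2.2-2.9 | 16-25% |
| HbA1c (mmol/mol) | 3 | 6.6-8.7 | 2.2-2.9 | 16-25% |
| Depression (points) | 0.75 | 1.7-2.4 | 2.2-3.2 | 14-24% |

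Taking the lower limit of the SD of change instead, the change-score ratio for HbA1c and systolic pressure is still about 2.1.

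**The case against.** **The arithmetic is right; the input is at fault.** This stands. Table 2 reproduces under 0.90. The fault is a correlation carried over without being stated or justified for each outcome.

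**Thirteen uncontrolled patients do not establish true values.** This stands too. A reader might infer that the true detectable differences are three times the table throughout. The documents do not support that. The pilot conflicts with 0.90 but does not fix a replacement. The threefold figure belongs to some outcomes under the change-score method; baseline adjustment caps it at about 2.2.

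**The planned longitudinal model could do better.** It might. If the effect were averaged over four follow-up visits with baseline adjustment and equal correlations (an assumption), the detectable difference would be 0.5547 × √((1 + 3r)/4 − r²), about 0.30 to 0.35 SD for r from 0.15 to 0.7. That is 1.2 to 1.4 times the table. Statistical analyses does not say that the effect will be averaged, and the table follows from the two-time-point method, so this shows sensitivity to method and does not rescue the figures.

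**The implied correlations mix pilot SDs of change with Table 2's SDs.** They do, and the value for HDL shows that the sources may not match. The change-score differences do not use Table 2's SDs, so they escape this. HDL should not be relied on. Nor should the exact insulin figure: the interval's midpoint is 51.0 but the means differ by 50.0, and if only 9 or 10 insulin users contributed (an assumption), the change-score detectable difference is 32-34 IU instead of 40. Either is far above 12.5.

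**The pilot interval includes the diet and its medication changes.** So does the trial's: Outcome assessment puts the baseline for these outcomes before the diet. Whether correlations at 2 years are higher or lower than at 4 months, the documents do not settle.

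**Conclusion.** The point holds as a should-fix item. Table 2 depends on a correlation of 0.90 for every outcome, and the protocol's own pilot contradicts it for the ten outcomes covered, LDL only marginally. On pilot variability the table is too small by a factor of about 1.4 to 1.6 for waist, LDL and diastolic pressure. For HbA1c, systolic pressure and depression the factor is about 2.2 (adjusted) to about 3 (change score). Insulin dose is inflated to a similar degree, without a secure figure.

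This rests on two-sided testing, 13 patients per row as Table 5 states, 4-month variability standing in for 2-year variability and, for the adjusted figures and implied correlations, Table 2's SDs.

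Two further inferences would go too far. The eight outcomes without pilot data (anxiety, self-esteem, the four CIS scales, EQ-5D and EQ-VAS) are not shown to be wrong; 0.90 is merely unsupported there. And the primary sample size is not in doubt: it reproduces, and the pilot supports 0.90 for weight.

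**What to change.** Recompute Table 2 with an outcome-specific correlation, estimated from pooled, arm-blind data of the patients already randomised, using whatever follow-up exists. The sample size section says that 75 had been randomised when the calculation was made. Pooled estimates involve no comparison of arms, so they do not breach the plan to hold no interim analyses.

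If such data are not available, show the detectable differences over a range that covers the pilot values, about 0 to 0.8. With 52 per arm that is 0.78 to 0.35 SD by change score, or 0.55 to 0.33 SD with baseline adjustment.

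State the correlation and analysis method behind each figure. Replace the statement that the sample size seems adequate for these outcomes with one that matches the recomputed table.

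The cost is a less favourable table. Neither trial conduct nor sample size changes.

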### Blinding

Given the nature of the intervention, it is impossible to blind the participants, CPI-therapist and researcher ([name]). Nevertheless, we will try to keep the intervention as separate as possible from the diabetes treatment, by giving participants strict instructions not to communicate about the intervention with their medical team. Patients are given the possibility to discuss problems related to the study with an independent medical doctor. The CPI group sessions will take place in another part of the hospital, outside the diabetes clinic, to ensure that patients and medical team will not run into each other. The VLCD is not a part of the intervention and can therefore be guided by the diabetes medical team.

To avoid bias, measurements will be conducted by blinded medical assistants and analyses will be done by two analysts, independent of each other.

The allocation sequence will be revealed to the researchers once recruitment, data collection and analyses are complete.

### Interventions

#### Phase 0: very Low calorie diet

The first part of the study (before randomization) is the same for all participants and consists of a Very Low Calorie Diet (VLCD) for the duration of 8 weeks, with a phase-out of 12 weeks. When after 8 weeks of VLCD a loss of 5% or more of the initial bodyweight is reached, random allocation to the intervention- and control group will take place. Patients losing less then 5% of bodyweight in the first 8 weeks are excluded from the study and will receive usual care, including dietary advice.

The use of a VLCD is an integrated part of the dietary treatment at our outpatient diabetes clinic. Normally, the patients are free to choose between the different types of weight reduction strategies. In the present study however, only one type of weight reduction therapy is used (VLCD).

The product we use for this study is Glucerna SR®, a product specifically developed for patients with diabetes and based on a combination of slow released carbohydrates, a low-fat, high monounsaturated fatty acid content and the addition of dietary fibre. Various studies indicate that this product decreases the postprandial blood glucose levels, which may have a lowering effect on HbA1c. This diabetes-specific diet product is also used as a meal replacement for achieving weight reduction in people with type 2 diabetes, with positive effects on weight control, glycaemic control and lipid profile [46-48]. We have chosen to use a twice a day regimen of meal replacements, together with a small dinner, providing 750 kcal, 67 g carbohydrates, 54 g protein and 32 g fat (of which 16 g monounsaturated fatty acids (MUFA)) a day and RDA recommendations in micronutrients. We believe that enabling the participants to have dinner with their family during the VLCD will improve compliance.

We have developed a protocol for the use of a VLCD in patients with type 2 diabetes, where we describe the different aspects of the treatment. Oral anti-diabetic agents (except Metformin) and short-acting insulin analogues are discontinued, while the dosage of long-acting insulin analogues and biphasic mixtures is halved, to avoid severe hypoglycaemia. GLP-1 or DPP-4 inhibitors will be continued. During the VLCD and gradual transition to a normal diet, medication is adjusted by means of glucose self-control and frequent contact with diabetes nurses and dieticians. The dose of any antihypertensive medication is also adjusted during VLCD and follow-up, in consultation with the responsible physician.

Realimentation takes place by slowly reintroducing normal food in 12 weeks time, until participants use a lightly energy restricted diet (1300 kcal a day), according to national dietary guidelines. 

#### Phase 1: control group

Following the VLCD-period and gradual reintroduction of normal diet, the control group receives usual care, provided by the diabetes team of the out-patient diabetes clinic of the Erasmus Medical Centre. Usual care consists of a 3-monthly visit to the physician and diabetes nurse, including medical examinations. Dietary treatment is part of usual care by referral to a specialized dietician. Patients are free to make additional appointments with their dietician in- or outside the hospital and they can choose to follow whatever diet they would like during the follow-up period. Both the number of visits to a dietician and the dieting methods, products and duration of the diet are noted during the follow-up period of 2 years. Dieticians in our hospital are all trained in motivational interviewing to motivate the patients in changing their lifestyle. All members of the diabetic team encourage the patients to get enough exercise, but we do not refer to an exercise programme. Patients in need of psychological help (ie psychological disorder, clinical depression, major eating disorder) are referred to a clinical psychologist in- or outside the hospital. In our population, these referrals are rare. Nonetheless, the number of visits to a psychologist as well as to other caregivers will be noted during this trial. CBT or techniques of PST and PC are no part of usual care.

**Weekly sessions**	
Session 1	Introduction of the therapist and the group members
	Agreements on attendance, commitment, homework and privacy
	Setting realistic treatment goals
	Explaining the rationale of the cognitive treatment
	Introducing relevant concepts op CBT (situation, thoughts, emotions, behavior) and the use of the diary
Sessions 2 – 4	Discussing rationale and the concepts of CBT
	Explaining unrealistic and automatic thoughts
	Identifying and challenging dysfunctional cognitions about eating, weight and shape (by Socratic dialogue)
	Homework: cognitive diaries
Sessions 5 – 8	Introducing the behavioral experiment
	Challenging dysfunctional cognitions by setting up a behavioral experiment
	Identifying and challenging ‘core beliefs’, the underlying self-schemas
	Homework: cognitive diaries and behavioral experiments
Sessions 9 – 10	Preparing for the oncoming ending of weekly sessions
	Identifying and challenging dysfunctional cognitions about relapse
	Introducing relapse prevention sessions
**Relapse prevention sessions**	
Session 11	Challenging dysfunctional cognitions about relapse
	Setting goals for the long term
	Explaining Problem Solving Treatment and Proactive Coping
Session 12 – 16	Implementing PST and PC in an individual plan
Session 17	Preparing for treatment ending
	Challenging dysfunctional cognitions about treatment ending
	Personal reminder in difficult times

After session 1, the structure of each session is as follows:

– time for questions following the previous session

– discussing home-assignments

– explaining and practicing of cognitive (behavioral) techniques

– discussing new home-assignments

– summary and evaluation of the session (by completing the Session Rating Scale)

In sessions 1–5 dysfunctional cognitions about eating, weight and shape are identified and challenged. Also exercise will be included in the sessions. Cognitive diaries are introduced and participants are encouraged to use these diaries at home to record personal critical situations and dysfunctional thoughts. They also score the credibility of their dysfunctional thoughts (0-100%). Furthermore, the validity of the dysfunctional thoughts is tested and alternative thoughts are generated. Guided by examples of the group, the group is acting as a research team, investigating the validity of dysfunctional cognitions and creating alternative and more realistic thoughts. The new thoughts are again scored on credibility (0-100%). Methods used for testing the validity of a person’s thoughts are the Socratic dialogue and behavioral experiments. Behavioral experiments are set up during the session, carried out at home, and discussed in the next session.

The underlying schemas (‘core beliefs’) are explored during sessions 6–10. The validity of self schemas is tested in the same way as the other dysfunctional thoughts and recorded in the diary.

Subsequently, 7 relapse prevention meetings are held to stabilize behaviour change, with increasing intervals until the end of the study (2 years). During these relapse prevention meetings, the acquired techniques will be repeated. In addition, techniques of Problem Solving Therapy are used to help participants coping with everyday problems they encounter while implementing their lifestyle changes. Based on individually set goals, experienced problems are identified and possible solutions will be put forward in a group brainstorm session. The participant will choose the most appropriate solution and creates and carries out an implementation plan. In this plan, the participant formulates the solution as a SMART (Specific, Measurable, Attainable, Realistic, Timely) goal and considers which steps should be taken to achieve this goal. Subsequently, the participants will be encouraged to identify barriers that may arise while trying to achieve their goals. Under guidance of the psychologist, activities will be defined which can be undertaken to prevent the occurrence or diminish the effect of these potentially threats (Proactive Coping).In following relapse prevention sessions, the implementation plan is evaluated and new (sub) problems are chosen to tackle. By linking Problem Solving Therapy to Proactive Coping and cognitive restructuring of (relapse) thoughts, we hope to have created a powerful intervention to provide participants skills to prevent and cope with relapse in their behaviour.

### Outcome assessment

Outcome measurements (see below) are assessed at baseline (before start VLCD), and again at 4 months (after VLCD and 10 CPI sessions), 1 year, 1 ½ years and 2 years.

Demographic variables are assessed at baseline by use of a self-administered questionnaire, which is checked during the intake interview with the investigator.

All other secondary outcomes are assessed at baseline, after 4 months, 1 year, 1 ½ years and 2 years, using self-administered questionnaires, except of the Session Rating Scale, which is filled in after every CPI session.

Data are managed by use of the trial management system ‘EXPeRT Clinical’ of OmniComm, USA.

#### Primary outcome

The primary endpoint with respect to the efficacy of CPI is the differential course of weight (kg) between both study groups, measured at 8 weeks and at 2 years follow-up. Weight is measured to the nearest 0.1 kg, after removal of shoes using a Seca 888 compact digital flat scale.

#### Secondary outcomes

1. Anthropometric measurements: Height is measured to the nearest 0.5 cm without shoes using a Seca stadiometer. Body Mass Index is calculated as weight divided by height squared (BMI = weight (kg)/height (m)^2^). Waist circumference (cm) is measured at the level midway between the lowest rib margin and the aliac crest. Hip circumference is measured at the widest point over the buttocks. Both waist- and hip circumference are measured by the nearest 0,5 cm, using a tape-measure. Subsequently, waist-hip ratio (WHR) is calculated.

2. Cardiovascular riskprofile by use of the UKPDS risk engine [49]:

a. Systolic and diastolic blood pressure (mmHg) are measured twice in upright position, while the patient had rested for at least 5 minutes with an Omron M4-I Intelli-sense device. The second value will be used.

b. Blood samples are taken to asses total cholesterol, LDL-cholesterol, HDL-cholesterol and triglycerides (mmol/l), measured on a Roche Modular P 800, reagents used from Roche, methods used from Roche are Cholesterol Chod-pap, HDL-c plus 3^rd^ generation, LDL-c plus 2^nd^ generation and Triglycerides GPO-PAP.

3. Glycaemic control:

a. HbA_1c_ (mmol/mol), measured on a Menarini HA-8160, reversed-phase action exchange chromatography.

b. HOMA-%S calculated by measuring fasting plasma glucose (mmol/l), (measured on a Roche Modular P 800, reagent used from Roche, method used from Roche is Glucose Hexokinase) and fasting insulin (mmol/l)

c. Glucose lowering medication (insulin (IU/day) and antidiabetic agents (mg/day))

4. Psychological measurements

a. Anxiety and depression are measured by the Hospital Anxiety and Depression Scale (HADS)[50,51]. The HADS consists of a 7-item Anxiety scale and a 7-item Depression Scale. The items are scored from 0 to 3 and the range of scores is 0 – 21. A score between 0 and 7 excludes depression/anxiety. A score of 8–10 indicates a possible depression/anxiety. A score of 11–21 is indicative of a probable depression/anxiety.

b. Somatic symptoms are measured by the VOEG-13 (‘Vragenlijst Onderzoek Ervaren Gezondheid’) [52], a Dutch 13-item questionnaire used to measure the health of a population, often used in social science research. The items consist of somatic symptoms like headache, nervousness and lethargy and respondents indicate whether they have these symptoms or not. A higher score indicates more somatic symptoms and a worse perceived health.

c. Fatigue is measured by the Checklist Individual Strength (CIS) [53], which quantifies subjective fatigue and related behavioral aspects. The CIS consists of 20 statements for which the respondent has to indicate on a 7-point scale to what extent the particular statement applies to him or her (1 = Yes, that is true; to 7 = No, that is not true). The statements refer to four fatigue aspects: (1) subjective fatigue (2) reduced motivation (3) reduced activity and (4) reduced concentration. For the CIS a cut-off point of >76 has been established [54]. People with a score above this cut-off point are at an increased risk of long-term sickness absence.

d. Self-esteem is measured by the Rosenberg Self-Esteem Scale (RSE) [55]. The RSE is a 10-item questionnaire that measures global self-esteem. Items are scored on a 4-point scale. A higher score indicates a more positive self esteem. Scores below 21 indicate low self-esteem.

e. Eating disorders are measured by the Eating Disorder Examination-Questionnaire (EDE-Q) [56], a 36 item questionnaire that measures concerns about shape, weight and eating, restraint and binge eating. Subscale scores for restraint and shape, weight and eating concern range between 0–6. A higher score indicates more severe eating psychopathology. Because binge eating cannot be measured reliably by the EDE-Q, we use a questionnaire composed by Werrij, et al. [28] for diagnosing binge eating disorder (BED), based on the DSM-IV criteria for BED. BED is diagnosed when respondents report eating binges twice a week or more.

f. Session rating. How the participants value the sessions is measured by the Session Rating Scale (SRS) [57]. The SRS is an ultra brief alliance measure designed specifically for every session clinical use. The SRS consists of four 10-cm visual analogue scales (relationship scale, goals and topic scale, approach or method scale, overall evaluation scale), with instructions to place a hash mark on a line (continuum) with negative responses depicted on the left and positive responses indicated on the right. Based on a total possible score of 40, any score lower than 36 overall, or 9 on any scale, could be a source of concern and therefore prudent to invite the client to comment.

5. Lifestyle

a. We developed a lifestyle questionnaire on diet history, smoking, drinking habits, drug use and hours sleep. (Additional file 1)

b. Physical activity is measured using the SQUASH (Short Questionnaire to Assess Health Enhancing Physical Activity) [58]. The SQUASH collects days per week, average time per day, and effort for physical activities such as commuting activities, leisure time and sport activities, household activities, and activities at work or school. Total minutes of activity are calculated for each question by multiplying frequency (days per week) by duration (minutes per day). Activity scores for separate questions are calculated by multiplying total minutes of activity by an intensity score (range 1–9). The total activity score is calculated by taking the sum of the activity scores for the separate questions.

6. Cost-effectiveness

a. Quality of life is measured by the EuroQol (EQ-5D) [59,60]. The EQ-5D is 5-item self report questionnaire on which participants report if they experience any problems in mobility, self-care, usual activities, pain and anxiety/depression. Each dimension has 3 levels: no problems, some problems and severe problems. The scores on the three dimensions can be combined into one co called ‘utility’ score, which represents the societal value of quality of life. The utility score has a range from 1.00 (the value of health without health problems) till 0.00 (the value of health problems as bad a death). This societal value of quality of life is used as input for so called Quality Adjusted Life Years (QALY) analysis, as the societal perspective is the preferred perspective in health economics. The EuroQol instrument contains also the EQ-VAS, a vertical visual analogue scale with the anchors best imaginable health (score of 100) and worst imaginable health (score of 0). This EQ-VAS represents the patient’s perspective of quality of life.

b. Costs are measured by the Trimbos/iMTA Questionnaire for Costs associated with Psychiatric Illness (TiC-P) [61]. The TiC-P measures direct medical costs due to healthcare utilization during the past four weeks. Also, it registers the indirect non-medical costs due to productivity loss during the past two weeks.

